### Measurements

Tests and measures used in the current study and time points at which they are administered are listed in Table 3. These are categorised as self-report questionnaires, clinical assessments, or computer-based tests.

**Table 3 Tab3:** Measures

Measurement domain	Measurement tool	Time points	Research question^a^/justification for use
Self-report measures			
Pain and symptom interference	Current pain intensity (Item 6 of the Brief Pain Inventory)	Weeks 1, 4, 7, 11, 19 & 31	RQ1, RQ3, RQ4, RQ5; group matching on baseline pain
	Brief Pain Inventory^b^ (BPI; short form; pain intensity and interference) [42]		RQ2, RQ3, RQ4, RQ5
	Pain Detect Questionnaire [43]		RQ2, RQ3, RQ4, RQ5
	Average pain intensity (Logbook)	Weeks 1 to 11 (daily)	RQ2, RQ3
	Average symptom interference (Logbook)		RQ2, RQ3
Physical functioning	Average range of movement (Logbook)	Weeks 1 to 11 (daily)	RQ2, RQ3
	Edinburgh Handedness Inventory (current and change) [44]	Week 1	RQ4, RQ5; participant characteristics
Body representation	Bath CRPS Body Perception Disturbance Scale (BPDS) [45]	Weeks 1, 4, 7, 11, 19 & 31	RQ2, RQ3, RQ4, RQ5
Emotional functioning	Tampa Scale for Kinesiophobia^b^ [46]	Weeks 1, 4, 7, 11, 19 & 31	RQ2, RQ3, RQ4, RQ5; group matching on baseline fear of movement
	Profile of Mood States [47]		RQ2, RQ3, RQ4, RQ5; group matching on baseline mood disturbance
	Revised Life Orientation Test [48]	Week 1	RQ4; group matching on baseline levels of optimism
Treatment expectations	Patient-Centred Outcomes Questionnaire [49]	Week 1	RQ4; group matching on expectations of treatment outcomes
Impression of treatment outcome	Patient’s Global Impression of Change [50]	Weeks 7, 11, 19 & 31	RQ2, RQ3
Treatment adherence	Treatment sessions (Logbook)	Weeks 4 to 6 (twice-daily)	Monitoring treatment adherence
Clinical assessments			
CRPS diagnosis	Budapest diagnostic research criteria assessment [51]	Weeks 1, 4, 7 & 11	Verification of CRPS diagnosis and assessment of eligibility
Symptom severity	CRPS severity score [52]	Weeks 1, 4, 7 & 11	RQ1, RQ3, RQ4, RQ5; group matching on baseline symptom severity
Autonomic functions	Limb temperature asymmetry	Weeks 1, 4, 7 & 11	RQ2, RQ3, RQ4, RQ5
	Oedema		
Motor functions	Grip strength	Weeks 1, 4, 7 & 11	RQ2, RQ3, RQ4, RQ5
	Δ Finger-To-Palm distance (ΔFTP)		
Sensory functions	Mechanical Detection Threshold (MDT)	Weeks 1, 4, 7 & 11	RQ2, RQ3, RQ4, RQ5
	Mechanical Pain Threshold (MPT)		
	Mechanical Allodynia		
	Two-Point Discrimination [53]		
Computer-based tests of neuropsychological changes			
Visuospatial attention	Visual Temporal Order Judgement (TOJ) task [8]	Weeks 1, 4, 7 & 11	RQ2, RQ3, RQ4, RQ5
	Landmark task [54]		
	Greyscales task [55]		
Mental representation of space	Mental Number Line Bisection task [56]	Weeks 1, 4, 7 & 11	RQ2, RQ3, RQ4, RQ5
Spatially-defined motor function	Directional Hypokinesia task [57]	Weeks 1, 4, 7 & 11	RQ2, RQ3, RQ4, RQ5
Body representation	Hand Laterality Recognition task [58]	Weeks 1, 4, 7 & 11	RQ2, RQ3, RQ4, RQ5

^a^RQ1, effects of treatment on the primary outcome measures; RQ2, effects of treatment on the secondary outcome measures; RQ3, time course / duration of any changes; RQ4, predictors of CRPS progression over time and/or response to treatment; RQ5, baseline abnormalities in neuropsychological functions in participants with CRPS compared to pain-free controls, and their relationships with clinical signs of CRPS (only Week 1 data)

^b^Brief Pain Inventory interference subscale and Tampa Scale for Kinesiophobia are also considered proxy measures of physical functioning

#### Baseline descriptors

Age, sex, and handedness of all the participants are recorded as demographic characteristics. An interview regarding their medical history is conducted to collect information about the date and type of any inciting injury or insult, CRPS duration in months from diagnosis to RS1, the presence of CRPS in body parts other than the primarily affected upper limb, the presence of non-CRPS pain conditions and other co-morbidities, and current treatments.

A hand laterality index is calculated using the Edinburgh Handedness Inventory [44] in RS1. The scoring can range from − 100 (extreme left-handedness) to 100 (extreme right-handedness). All participants respond regarding their current hand preference, and the participants with CRPS additionally complete another version of the Edinburgh Handedness Inventory based on their recalled hand preference prior to the onset of CRPS symptoms. A “change in handedness” score (Handedness after CRPS – Handedness before CRPS) is calculated to give an approximation of the functional impact of the CRPS.

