### Participants

#### Eligibility criteria

##### Participants with CRPS

This study enrols both male and female individuals, who:
are willing and able to give informed consent to take part in the trial,are aged 18–80,have a diagnosis of CRPS type I based on the Budapest diagnostic research criteria [2] as assessed at RS1 and revisited at RS2,have CRPS type I primarily affecting one upper limb,have had CRPS for a minimum of 3 months at the time of RS1,and report current pain intensity ≥2 on a 0–10 Numeric Rating Scale at RS1 and RS2.

Participants are excluded from the CRPS group if they:
lack sufficient English language ability to provide informed consent,are classified as legally blind,have a history of neurological disorder (e.g. stroke, neurodegenerative disease or traumatic brain injury),have CRPS meeting the Budapest diagnostic clinical or research criteria affecting both sides of the body,^2^report that they have confirmed presence of nerve damage (CRPS type II) based on the results of nerve conduction test,have dystonia or any other physical limitation severe enough to prevent satisfactory execution of PA/sham treatment,or have a severe psychiatric comorbidity (such as schizophrenia) that in the researchers’ opinions would compromise participation in the study.

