### Randomisation

Treatment allocation is conducted by method of randomisation with stratification to minimise baseline (RS1) group differences. Eligible participants with CRPS are allocated in equal numbers to one of the two treatment groups: PA treatment group or sham treatment group. Group allocation is performed using MINIM computer programme [34] by a researcher who is not involved in data collection ([name]). The minimisation procedure controls for the stratification factors that are listed in Table 2. In the event of participant’s withdrawal after treatment allocation, but before RS3, their data shall be removed from the minimisation procedure and an additional participant shall be recruited for the trial to ensure equal numbers of full datasets with any post-intervention data in the two groups.

**Table 2 Tab2:** Criteria for stratification as recorded in RS1

Factor	Weight	Categories
Current pain intensity (0–10 Numerical Rating Scale)	2	≤ 6
		> 6
CRPS severity score (1–16) [35]	2	≤ 12
		> 12
Primarily affected arm	1	Left
		Right
Pre-CRPS dominant hand (writing)	1	Left
		Right
Sex	1	Male
		Female
Age	1	18 - < 40
		40 - < 61
		61–80
Presence of CRPS in body parts other than the primary affected arm	1	Yes
		No
Presence of other non-CRPS pain	1	Yes
		No
CRPS duration	1	< 1 year
		1 - < 5 years
		5 - < 10 years
		≥ 10 years

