##### Computer-based/psychophysical tests

Six computer-based measures are used in the present study to assess the following neuropsychological functions: visuospatial attention, cognitive representation of space, spatially-defined motor function, and body representation. To test for spatial attention bias in near space, we administer versions of three tasks that have been used to measure spatial attention in hemispatial neglect: a visual Temporal Order Judgement (TOJ) task [8], a Landmark task [54], and a Greyscales task [55]. The fourth task is a Mental Number Line Bisection task, which measures the mental representation of space [56, 81]. The fifth task is a Directional Hypokinesia task, a measure of motor “neglect-like” impairment. The final computer-based task is a Hand Laterality Recognition task, which is thought to be indicative of body representation [58].

All measures presented in this section are collected in RS1-RS4 from the participants with CRPS and during a single research session from healthy control participants. Hand and side of space for all tasks are coded as affected or unaffected (for controls, the “affected” and “unaffected” hand / side is coded based on their matched participant with CRPS). Each task is preceded by a short practice session to familiarise the participant with the task. If they do not appear to follow the instructions during practice, these are explained again, and the practice is repeated.

***Visuospatial attention*** The following three computer-based tests are used to measure visuospatial attention: the visual TOJ task, the Landmark task and the Greyscales task.

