#### Predictors of the response to PA treatment and/or CRPS progression over time (RQ4)

We will conduct exploratory analyses of the potential factors that can predict response to treatment for the PA group. First, we will calculate reduction scores as a change in current pain scores and CRPS severity scores from the immediate pre-treatment to immediate post-treatment sessions (RS3 – RS2). Second, we will conduct two separate linear mixed models regressions on pain reduction scores and CRPS severity reduction scores including the pertinent explanatory factors such as demographic characteristics; current pain intensity; CRPS severity score; and scores on the self-report questionnaires, clinical assessments, and computer-based tests. In the first instance, we will consider those outcomes that differed the most from the healthy control participants in RS1 (see statistical analyses for RQ5 in the next section).

The same factors will be considered potential explanatory variables in linear mixed models regressions on current pain scores and CRPS severity scores across four research sessions (RS1-RS4). These exploratory analyses will be conducted for data from all the participants with CRPS to examine possible predictors of CRPS progression over time (including but not limited to treatment group).

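### The change-in-handedness score is signed left-right, so the same shift away from the affected arm scores negative in right-arm and positive in left-arm CRPS, and its link with functional impact is attenuated if the two sides are pooled (minor)

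*Protocol article*

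**What the plan says.** Baseline descriptors (Protocol article) gives the range of the laterality index, with the poles described as "extreme left-handedness) to 100 (extreme right-handedness". Participants with CRPS complete the inventory for current preference and again for recalled preference before onset. The change-in-handedness "score (Handedness after CRPS – Handedness before CRPS) is calculated to give an approximation of the functional impact of the CRPS".

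Eligible participants "have CRPS type I primarily affecting one upper limb", left or right. Table 2 lists "Primarily affected arm" (left/right) as a minimisation factor.

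Table 3 lists "Edinburgh Handedness Inventory (current and change") under physical functioning at week 1. It assigns the measure to RQ4 and RQ5 as well as to participant characteristics. The RQ4 section takes candidate explanatory factors from demographics, pain, severity and "scores on the self-report questionnaires, clinical assessments, and computer-based tests".

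Other lateralised measures are tied to the affected side. For the computer-based tests, "Hand and side of space for all tasks are coded as affected or unaffected". The Greyscales and number-line scores are re-expressed in the same way, and grip strength and finger-to-palm change are affected/unaffected ratios. No such step is stated for the change-in-handedness score.

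**The concern.** A measure of functional impact should take the same value for the same loss of use, whichever arm is affected. A right-positive index with a plain after-minus-before difference cannot do this. Less use of an affected right hand lowers the index, and less use of an affected left hand raises it.

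If such a score is averaged, regressed on or correlated across both sides, two things happen. It becomes largely a marker of the affected arm, and the opposite slopes in the two sides pull the pooled association towards zero. Functional impact could then look unrelated to course, response or neuropsychological change because of the coding alone. Minimising on affected arm balances the sides between treatment groups but leaves both sides mixed within each group. A main effect for affected arm would not repair the predictor either, because the slopes differ in sign. That would take an interaction or a recode.

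**Working it through.** The plan states no figure for this score, so there is none to reproduce. The scale and formula come from Baseline descriptors. The index values, shifts, handedness shares and left/right mixes below are assumptions.

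**Step 1. The formula as written: score = after - before.**
- Right-arm CRPS, +80 to +20: 20 - 80 = -60.
- Left-arm CRPS, -80 to -20: -20 - (-80) = +60.
- Starting from 0, the same 60-point shift gives -60 (right arm) or +60 (left arm).

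Equal loss of use gets opposite signs. This follows from the stated scale and formula and needs no assumption about the sample.

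**Step 2. Pooled mean if all 42 participants lose 60 points: (R × -60 + L × 60) / 42.**
- 21 right, 21 left: 0.
- 25 right, 17 left: (-1500 + 1020) / 42 = -11.4.
- 29 right, 13 left: (-1740 + 780) / 42 = -22.9.
- 42 right: -60.

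Re-signed to the affected side, the mean is 60 in every case.

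**Step 3. The ±100 bound.** A right-hander at +80 with left-arm CRPS can move at most +20. With 21 right-handers per side, losing 60 (right arm) or 20 (left arm), the pooled mean is (21 × -60 + 21 × 20) / 42 = -20 as written. Recoded, it is (21 × 60 + 21 × 20) / 42 = +40. Unequal shifts therefore leave partial rather than full cancellation.

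**Step 4. Simulated association.** Assumptions: pre-CRPS index magnitude mean 80 (SD 15); intended shift away from the affected hand mean 50 (SD 30); index bounded at ±100; 90% right-handed; half right-affected. There were 400,000 simulated participants per scenario.

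| Quantity | As written | Recoded to affected side |
|---|---|---|
| Mean, right-arm | -47 | +47 |
| Mean, left-arm | +21 | +21 |
| Pooled mean | -13 | +34 |
| Correlation with the simulated shift | -0.22 | +0.62 |

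- The as-written score correlates about -0.8 with right-arm involvement, so it mainly encodes side.
- Across 40-60% right-affected and 80-100% right-handed, the correlation with the shift runs from -0.09 to -0.37 as written, against +0.56 to +0.68 recoded.
- If the dominant hand is affected in everyone and sides are equal, the as-written correlation is about 0.

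**Step 5. Where the score is used.**
- Descriptive characteristics lists it per individual participant, alongside the affected limb.
- The CRPS-control contrast under RQ5 uses pre-CRPS handedness in the patients and current handedness in controls, so the change score does not enter.
- The RQ4 section looks first at outcomes that differ most from controls, and the RQ5 correlations depend on significant differences from controls. Controls complete only the current version, so they have no change score and it cannot pass either screen.
- The remaining route to pooled use is the Table 3 assignment to RQ4 and RQ5, together with an RQ4 factor list that is open-ended.

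**The case against.** The strongest reply accepts the arithmetic and disputes the reach, and most of it stands.

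- **Use.** The only analysis section that names the score lists it per person next to the affected limb. Nothing is pooled there and the reader can see the direction. A reader might infer from Table 3 that the score is certain to enter the RQ4 regressions and RQ5 correlations. The documents support only that it may, since those sections do not name it and it cannot pass their control-difference screens.
- **Cancellation.** A reader might infer that the score cancels out. In general it does not: the main scenario above leaves a pooled mean of -13 and a correlation of 0.22 in absolute size. The general effect is attenuation plus confounding with side.
- **Direction.** Setting -0.22 against +0.62 suggests a reversed finding. Part of that contrast is convention, because after minus before makes loss of right-hand use negative. The fair comparison is 0.22 against 0.62 in absolute size.
- **Stakes.** This is a week-1 descriptor described as approximate, and RQ4 and the RQ5 relationship analyses are declared exploratory. Both indices and the affected side are recorded, so the score can be re-signed at any time without loss of data.

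None of this rescues the definition. The article states both a formula and a purpose, and the formula does not serve the purpose when both arms are enrolled. It is a stated formula, so it is not a detail merely left to an analysis plan.

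**Conclusion.** Wrong as written, and minor. The sign reversal between right-arm and left-arm CRPS is certain from the stated scale and formula, and the document does not correct it.

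The consequence is conditional on the score being summarised or modelled across both sides. In that case its absolute correlation with functional impact is roughly 0.1 to 0.4 as written, against 0.55 to 0.7 recoded. It comes near zero only when sides and shifts balance. These sizes rest on assumed index values, shifts, handedness and side mix; only the sign reversal is free of assumptions.

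The primary outcomes, the treatment comparison, the individual listing and the CRPS-control handedness contrast are untouched. The documents do not support reading this as a threat to the efficacy analysis or as a planned analysis that is bound to fail.

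**What to change.** In Baseline descriptors, define the score as shift away from the affected hand:
- right arm affected: before - after;
- left arm affected: after - before.

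Positive values then always mean less use of the affected hand. Use this version wherever the score is summarised or modelled, including any RQ4 or RQ5 analysis that Table 3 allows.

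Optionally, add an indicator for whether the dominant hand is affected, because the ±100 bound limits the possible shift when it is not. This is a separate refinement and not needed to correct the sign.

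The cost is one line of recoding from the affected side already recorded for minimisation, with no new data. The optional indicator adds one term to exploratory models.

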#### Primary outcomes

A change between RS2 (immediately before the commencement of treatment) and RS3 (immediately after the end of the treatment period) in current self-reported pain intensity and CRPS severity score [35, 52] are the primary outcomes. People with CRPS consider pain relief to be the highest priority for recovery [59], and pain intensity is the most common primary outcome in chronic pain trials [60]. Current pain intensity is measured using item 6 of the Brief Pain Inventory (BPI; short form) [42], which is a Numerical Rating Scale (NRS) ranging from 0 – “no pain” to 10 – “pain as bad as you can imagine”. The BPI has high reliability [42]. In addition to pain, CRPS involves a range of other debilitating symptoms, some of which were also affected by PA in previous studies [22, 24]. Therefore, we included a comprehensive measure of symptoms severity as the second primary outcome. The CRPS severity score assessment protocol follows the 16-points scoring system published by Harden and colleagues [35]. This continuous index of CRPS symptom severity has good discrimination abilities, concurrent validity and adequate sensitivity to change [35, 52], and has been recommended as one of the core outcome measures for CRPS clinical studies [61].

#### Secondary outcomes

##### Self-report questionnaires

There is a lack of validated outcome measures for CRPS (however, see recently published recommendations [62]). Therefore, the choice of the measures for the current trial was guided by general recommendations of core outcome measures for chronic pain clinical trials (IMMPACT [60];) and the existing literature on CRPS implicating other relevant questionnaires.

There are 10 self-report questionnaire measures of pain, physical and emotional functioning, body representation, expectations about treatment, and impressions of treatment outcome. The BPI [42], Pain Detect Questionnaire [43], Bath CRPS Body Perception Disturbance Scale (BPDS [45];), Tampa Scale for Kinesiophobia, and Profile of Mood States [47] are completed in every research session and long-term follow-up (RS1-RS4, LTFU1-LTFU2). A Revised Life Orientation Test [48] and a Patient-Centred Outcomes Questionnaire [49] are administered only in RS1. The Patient’s Global Impression of Change questionnaire [50] is completed only at post-treatment research sessions and long-term follow-ups (RS3-RS4, LTFU1-LTFU2). Finally, a daily logbook of self-reported average pain, range of movement, and symptom interference is kept by the participants during the baseline, treatment, and post-treatment periods (i.e., every day for the 10 weeks that elapse between RS1 and RS4).

Participants use the short-form of the BPI [42] to rate their pain intensity (current, average, and worst and least pain over the last 24 h) and the extent to which pain interferes with their physical, social and psychological functioning on 0–10 NRSs (0 – “no pain” or “does not interfere”; 10 – “pain as bad as you can imagine” or “completely interferes”, respectively). The pain intensity component of BPI can result in an average score between 0 and 10; an average interference component score can also range from 0 to 10. The Pain Detect Questionnaire is a validated measure of the neuropathic features of experienced pain [43] scored from − 1 to 38, with higher scores indicating a greater neuropathic component of pain.

The BPDS [45] includes seven self-reported items to assess subjective detachment, awareness, attention to, and feelings about the CRPS-affected limb; the perceived changes in size, temperature, pressure, and weight of the limb; and any desire to amputate the limb. The BPDS includes a mental imagery task in which the mental representation of both limbs (affected and unaffected) is sketched by a researcher based on the participants’ description. Total score ranges from 0 (no disturbance) to 57 (most severe disturbance of body perception). Since BPDS is not a validated measure, normative data is also collected from healthy control participants who are responding to the self-report components regarding the limb that corresponds to the CRPS-affected limb of their matched participant with CRPS.

The Tampa Scale for Kinesiophobia [46] is administered to measure pain-related fear of movement and re-injury. The participants choose the extent to which they agree with each of 17 statements about fear of movement and physical activity that could (subjectively) cause pain and/or injury (1 – “strongly disagree”, 4 – “strongly agree”). The final score varies from 17 to 68 points, with higher numbers indicating more severe kinesiophobia. The Tampa Scale for Kinesiophobia is included as a measure of the likely extent to which participants use their affected limb and their beliefs and emotions about those movements.

Considering that mood can exert effects on pain [63–65] and attention [66–68], the Profile of Mood States is administered in the current trial to verify that the two treatment groups are matched according to mood disturbance, and to enable evaluation of whether treatment results in any significant differences in mood improvements between the groups. The Profile of Mood States is a 64-item scale indicating the extent to which the respondent is experiencing various transient, distinct mood states (1 – “not at all”, 5 – “extremely”). High reliability and validity of Profile of Mood States [47, 69] has been reported. This measure is also completed by healthy control participants at a single research session.

The Revised Life Orientation Test [48] assesses levels of optimism and pessimism. Participants rate to what extent they agree with 10 statements on a scale from 0 – “strongly disagree” to 4 – “strongly agree”. The Patient Centred Outcomes Questionnaire [49] is also administered to measure patient-centred expectations and criteria for success in chronic pain treatment. Rating scales from 0 to 10 are used to indicate the usual, desired, expected and considered successful levels of pain, fatigue, emotional distress, and interference with daily activities (0 – “none”, 10 – “worst imaginable”), and the importance of improvement in each of these areas (0 – “not at all important”, 10 – “most important”). The decision to include the Revised Life Orientation Test and the Patient Centred Outcomes Questionnaire in the current trial was driven by the fact that optimism and expectations of outcome have been known to influence the success of novel treatments [70–72]. Thus, it is important to confirm that the two treatment groups are matched on these extraneous factors, or to include these variables as covariates in the analysis of outcome measures if they are not.

The participants keep daily logbooks for weeks 1–11 in which they use 0–10 NRSs to record their average level (over the preceding 24 h) of pain (0 – “no pain at all”, 10 – “pain as bad as it could be”), the range of movement in the affected arm (0 – “no movement at all”, 10 – “normal movement”), and the degree to which their symptoms have interfered with their daily life (0 – “no interference at all”, 10 – “complete interference”). These measures are designed to track the time-course of any change in pain, movement, and interference during the first 10 weeks of the study (i.e. four-week baseline period, two-week treatment period, and four-week immediate post-treatment period).

Finally, the Patient Global Impression of Change questionnaire [50] is administered to measure participants’ impression of how much their symptoms have changed due to treatment. It produces a single rating on a scale from 1 – “no change” to 7 – “a great deal better”. The Patient Global Impression of Change is a widely recommended measure of perceived global improvement and satisfaction with treatment [60, 62].

